## Background

Gonorrhoea is the second most common bacterial sexually transmitted infection (STI) in the UK, with 34,958 infections reported in 2014 [1]. A disproportionate burden of infection is seen in young adults and minority ethnic groups (35% of infections). The highest rates of infection are in large urban areas, and infection is concentrated in core high-risk groups such as men who have sex with men (MSM), black and minority ethnic (BME) groups, and those reporting multiple sexual partners. There has recently been a significant rise in rectal gonorrhoea in MSM thought to reflect an increase in unsafe sexual behaviour [2].

Gonorrhoea leads to local inflammation causing genital pain and discomfort, and the localised immune activation also facilitates the acquisition and transmission of HIV. In women, infection can spread to the fallopian tubes and ovaries causing pelvic inflammatory disease with resultant tubal scarring, infertility, chronic pelvic pain and an increased risk of ectopic pregnancy. In men, gonorrhoea can lead to epididymo-orchitis and, in men who have sex with men, gonococcal proctitis can lead to abscess and fistula formation. Pharyngeal infection, whilst usually asymptomatic, is an important reservoir of onward transmission in both women and MSM. It is also harder to treat with antibiotics [3] and can persist even when sensitivity testing suggests that it should be susceptible [3]. It is, therefore, important to find out whether treatment is effective for infection at all anatomical sites.

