### Why a trial is needed now

As the susceptibility of *N. gonorrhoeae* to currently recommended antibiotics decreases and multidrug-resistant strains become more common, it is important to demonstrate the efficacy and safety of alternative treatment regimens in patients with gonorrhoea. Gentamicin is a cheap and widely available antibiotic. It has been associated with renal and vestibulo-cochlear toxicity, which is partially dose-related [21], and the use of a single one-off dose appears to be well-tolerated [22]. In vitro microbial sensitivity data [23] support the use of gentamicin but there is need for clinical trial data to assess its efficacy and safety, particularly in pharyngeal and rectal infections.

Our hypothesis is that gentamicin is not clinically worse than ceftriaxone in the treatment of gonorrhoea. The aim is to test this hypothesis in a randomised trial by comparing microbiological clearance of *N. gonorrhoeae* following treatment with gentamicin or with ceftriaxone.

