### Sample size

Based on a cure rate of 96% for the ceftriaxone regimen, which is consistent with previous trials, a total sample size of 646 for analysis (323 in each group) will achieve a 90% power to detect noninferiority with lower confidence interval for an absolute risk difference of 5%. The one-sided significance level is 0.025. To allow for a loss to follow-up rate of up to 10%, the trial will recruit a total of 720 participants.

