### Statistical analyses

Demographic and clinical measures will be compared between the randomised arms at baseline using appropriate descriptive statistics for continuous and categorical variables.

The primary approach to between-group comparative analyses will be by intention-to-treat without imputation of missing outcome data. Sensitivity analyses will be conducted to investigate the impact of missing primary outcome data, using simple and multiple imputation. Due to both interventions being single-dose administered immediately following randomisation, nonadherence with treatment allocation is expected to be low. Therefore, additional sensitivity analyses that aim to estimate treatment effect amongst those who have adhered with allocation are not expected to be required.

The evaluation of the primary clinical outcome variable will be performed using a general linear model for binary outcome adjusted by clinic site. The primary efficacy parameter comparing gentamicin with ceftriaxone will be the difference in the proportion of participants clear of infection at 2 weeks follow-up along with the 95% confidence interval. Gentamicin will be regarded as noninferior if the lower 95% confidence limit for the risk difference in confirmed clearance is −5 percentage points or greater.

Secondary outcomes will be similarly analysed using appropriate regression models dependent on data type, adjusted for clinic site and baseline value of the outcome variable if collected. These analyses will be considered supportive to the primary analyses.

To explore treatment efficacy by site of infection, for each of the three infection sites, we will separately estimate clearance by treatment arm along with 95% confidence intervals, rather than formally fit an interaction term for the seven different possible combinations of infection site in the regression model. Any suggestion of a differential effect according to infected site would require confirmation in future research.

The relationship between clinical effectiveness and MIC will be examined visually.

Safety and tolerability analyses will be descriptive. Frequency counts and percentages of the prespecified main categories of AEs will be presented by treatment arm.

All planned analyses will be described in the Statistical Analysis Plan which will be finalised prior to database lock and unblinding of the trial.

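### Efficacy by infection site is to be shown only as separate per-arm clearance intervals, so the gentamicin–ceftriaxone difference is not estimated at any single site

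*Protocol article*

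**What the plan says.** In the Protocol article, Statistical analyses, the primary efficacy parameter is the between-arm difference in the proportion clear of infection, with a 95% interval and a −5 point limit. For infection site the plan changes form: for each of three sites "we will separately estimate clearance by treatment arm along with 95% confidence intervals, rather than formally fit an interaction term". The reason given is that infection site has seven possible combinations. The analysis is introduced as exploratory, and any differential effect is said to need confirmation in later research.

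Elsewhere the article gives infection site real weight. Background calls it "important to find out whether treatment is effective for infection at all anatomical sites" and says of pharyngeal infection: "It is also harder to treat with antibiotics". The section on why a trial is needed now asks for efficacy and safety data "particularly in pharyngeal and rectal infections". Participants says that some clinics were chosen to raise the number of pharyngeal and rectal infections. Baseline visit requires a full sampling profile so that efficacy can be assessed at each infected site, and Follow-up of participants re-swabs the sites that were infected.

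**The concern.** The quantity that randomisation supports at a site is the difference between arms among those infected there. Clearance in each arm with its own interval does not state that quantity or its uncertainty. A reader must compare two intervals by eye, and the natural habit of looking for overlap is much stricter than a 5% test.

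At stake is the extragenital information that the trial was partly set up and sampled to obtain. A moderate pharyngeal deficit of gentamicin could appear beside an overall noninferior result as two overlapping intervals, with nothing in the planned output saying how large the difference is or what range the data allow.

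The stated reason does not settle the matter. Seven combinations argue against a seven-level interaction. They do not argue against three simple contrasts, one for each site that the plan already tabulates.

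**Working it through.** **The plan's own figure.** Inputs from Sample size: "Based on a cure rate of 96% for the ceftriaxone regimen" (gentamicin taken as equal), 5-point margin, 90% power, one-sided level 0.025.

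n per arm = (1.960 + 1.282)² × 2 × 0.96 × 0.04 / 0.05² = 10.51 × 0.0768 / 0.0025 ≈ 323, so 646 in all. Allowing 10% loss, 646 / 0.9 ≈ 718, against 720 stated. The overall sample size reproduces. It is set for the overall comparison, not for any site.

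**One worked example.** Assumption, not in the documents: 100 pharyngeal infections per arm, 96 cleared on ceftriaxone and 87 on gentamicin.

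- Wilson interval: [p + z²/2n ± z√(p(1−p)/n + z²/4n²)] / (1 + z²/n), with z = 1.96.
- Ceftriaxone: (0.9792 ± 0.0429) / 1.0384 = 90.2% to 98.4%.
- Gentamicin: (0.8892 ± 0.0687) / 1.0384 = 79.0% to 92.2%.
- These overlap between 90.2% and 92.2%.
- Newcombe interval for the difference of −0.090: lower −0.090 − √((0.870 − 0.790)² + (0.984 − 0.960)²) = −0.173; upper −0.090 + √((0.922 − 0.870)² + (0.960 − 0.902)²) = −0.012.
- The difference interval, −17.3 to −1.2 points, excludes zero.

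**How strict is overlap?** With equal standard errors, two 95% intervals separate only when the difference exceeds 1.96 × √2 = 2.77 standard errors of the difference. That is a two-sided level of 2(1 − Φ(2.77)) = 0.0056.

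**Over a range of settings.** Simulation, 200,000 trials per setting, 323 analysed per arm. Assumptions not in the documents: pharyngeal share 20–50%, ceftriaxone clearance 96% at every site, and a gentamicin deficit of 10 points confined to those with pharyngeal infection.

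| Pharyngeal share (per arm) | Per-arm intervals separate | Difference interval excludes zero | One-term interaction significant | Overall noninferior and per-arm intervals overlap | Overall noninferior and difference interval includes zero |
|---|---|---|---|---|---|
| 20% (65) | 20% | 50% | 46% | 40% | 31% |
| 30% (97) | 38% | 68% | 61% | 20% | 15% |
| 40% (129) | 53% | 82% | 69% | 8% | 6% |
| 50% (162) | 66% | 90% | 74% | 3% | 2% |

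For a 5-point deficit, the chance of overall noninferiority with overlapping per-arm intervals is 69%, 56%, 43% and 31% across the same shares. For a 15-point deficit it is 17%, 4%, 1% and 0.1%.

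**What a site contrast cannot do.** If the arms are truly equal at 96%, power for noninferiority at 5 points within the pharyngeal group is Φ(0.05 / √(2 × 0.0384/m) − 1.96). This gives 31%, 43%, 54% and 63% for m = 65, 97, 129 and 162. With a 10-point deficit, the expected half-width of the difference interval is 9.7 points at m = 65 and 6.1 points at m = 162.

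**The case against.** The strongest reply is that the plan claims little here. Its hypothesis and decision rule concern overall noninferiority, and the site analysis is openly exploratory. The display would show both rates (96% and 87% in the example), nowhere makes overlap the criterion, and with counts printed anyone can compute the difference. The statistical analysis plan is not shown and may already include it. All of this stands as a limit on severity. It does not answer the point: an exploratory analysis should still estimate the randomised contrast, and a signal has to be visible before it can be sent for confirmation.

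Three stronger readings are tempting, and the documents do not support them.

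- A reader might infer that infection site is the trial's key question and that a pharyngeal deficit would be hidden. Site is a stated rationale, not the hypothesis. The primary outcome requires clearance at every infected site, so a pharyngeal failure counts as a primary failure. The deficit is diluted, not removed. Masking is mainly a risk at about 5 to 10 points, or with a small pharyngeal share, and the difference interval reduces it only modestly (40% to 31%, and 20% to 15%, in the first two rows of the table).
- A reader might infer that refusing the interaction is itself the mistake. Seven is the right count at participant level (2³ − 1), and even a single treatment-by-pharynx term has less power than the within-site difference interval in every row of the table.
- A reader might infer that the primary model is deficient without pharyngeal infection as a covariate. Omitting it does not bias a randomised comparison, and the model matches the stratification by centre. If pharyngeal clearance is 85–90% against 97% elsewhere (assumed), adjustment removes only about 2–5% of variance. Heterosexual men are not sampled at the pharynx (Table 1), and symptomatic participants are usually treated at the visit at which the swabs are taken, so site results often follow treatment.

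**Conclusion.** The concern holds in a narrow form. As published, the plan makes a deliberate choice to present infection site by arm only, and so gives no between-arm estimate at the genital, pharyngeal or rectal site. That is a weaker analysis than the same data allow. Under an assumed 10-point pharyngeal deficit, a difference interval excludes zero about 24 to 30 percentage points more often than the per-arm intervals separate.

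These sizes rest on assumed pharyngeal shares and site-specific clearance rates, because the article gives none, and on readers judging by overlap. The primary analysis and its sample size are unaffected. This is a worthwhile, low-cost improvement to an exploratory analysis, not a flaw in the trial's main conclusion.

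**What to change.** In Statistical analyses, and in the statistical analysis plan if it does not already say so, add: for each of the three infection sites, among participants infected there at baseline, report clearance at that site by arm together with the gentamicin-minus-ceftriaxone risk difference and its 95% interval, using a method suited to proportions near 100%, such as Newcombe's. Label these results exploratory. State that a participant infected at several sites enters more than one contrast, that intervals at the rarer sites will be wide, and that no site-specific noninferiority conclusion will be drawn.

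An interaction test and a supportive analysis adjusted for pharyngeal infection may be added but are not needed. If the latter is done, say how heterosexual men, who are not swabbed at the pharynx, are coded.

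The cost is one sentence and an extra column or two in a planned table. The swabs are already taken at baseline and follow-up. When the article was written recruitment was still open, and the analysis plan was due to be finalised only before database lock, so the change could be made before unblinding.

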### Trial management and oversight

Day-to-day management of the trial is the responsibility of the Trial Management Group (TMG), which meets at least every 2 months and more often if required. Trial oversight is by an independent Trial Steering Committee (TSC). Safety of trial participants is monitored by an independent Data Monitoring Committee (DMC), which reports to the TSC. The trial is coordinated by the NCTU.

## Discussion

The G-TOG trial is designed to be a pragmatic trial which aims to reflect routine NHS clinical practice and thus trial procedures, as far as possible, mirror routine clinical practice. Careful consideration and training was given during the set-up stage of the trial to ensure that maintenance of the blind was both feasible and practicable at each participating site without causing any additional burden of work for site staff. An initial assessment of current practice was conducted to identify any potential problems at each site in concealing treatment allocation from both participant and the blinded site research team. This included suitability of the areas where treatment is administered to ensure adequate privacy from any blinded members of the research team. Nurses administering treatment are trained on the importance of provision of consistent information to all participants, regardless of treatment allocation. Treatment administered to trial participants is obtained from standard clinic stock, thus it was also essential to consider whether access to the storage areas for drugs could also result in inadvertent unblinding.

A key challenge for site staff in recruiting patients into the trial is the need to ensure adequate availability of GCP and trial-trained staff since the trial demands both a blinded research nurse/physician and an unblinded nurse administering treatment to perform separate roles during the initial clinic visit. This has meant training a larger number of staff than would ordinarily be required for a trial of this size.

The trial is designed so that participants, clinicians and researchers are blinded to treatment allocation. Whilst the primary end point of the trial is objective and so not subject to bias from knowledge of treatment intervention, blinding to allocation is necessary to minimise selection bias at recruitment and to ensure that ascertainment of outcome and assessment of safety is not biased by knowledge of the administered treatment.

Gentamicin is not currently recommended for use in the UK to treat gonorrhoea due to a lack of efficacy and safety data. The results of this trial will assess whether gentamicin is not clinically worse than ceftriaxone for the treatment of gonorrhoea, when resistance to current antibiotics leads to clinical failure. The trial will generate knowledge about the efficacy of gentamicin in the treatment of gonorrhoea, both at genital and nongenital sites, extend our knowledge of the safety of single-dose gentamicin therapy and provide data to correlate laboratory-based sensitivity testing with the clinical response to treatment (thus helping to calculate the MIC ‘breakpoints’ which can be used to predict from laboratory testing whether a patient will respond to treatment).

It is expected that the results of the trial will inform future guidelines on the treatment of gonorrhoea, influence policy recommendations on antimicrobial testing and surveillance, and assist developing countries in choosing evidence-based affordable gonorrhoea treatment.

## Trial status

Recruitment to the G-TOG trial commenced in October 2014 and is expected to continue until the end of October 2016. So far, 593 patients have been randomised (as of 11 July 2016). At the time of writing, thirteen sexual health outpatient clinics in England were participating in the trial.

## Abbreviations

AC: Aptima Combo
AE: Adverse event
BASHH: British Association for Sexual Health and HIV
BD: Becton Dickinson
CI: Chief investigator
DMC: Data Monitoring Committee
GCP: Good Clinical Practice
MIC: Minimum inhibitory concentration
MSM: Men who have sex with men
NAAT: Nucleic Acid Amplification Test
NCTU: Nottingham Clinical Trials Unit
STBRU: Sexually Transmitted Bacteria Reference Unit
STI: Sexually transmitted infection
TSC: Trial Steering Committee
UHBFT: University Hospitals Birmingham NHS Foundation Trust
VAS: Visual Analogue Scale
